#### Prognostic model development

2.2.2

To develop and validate robust prognostic models that can identify infants at high risk for adverse outcomes. This includes creating models for the early prediction of severe NARDS (sNARDS) and for long-term prognosis.

#### Biomarker discovery and validation

2.2.3

To discover and validate novel biomarkers for NARDS by linking our longitudinal biobank to clinical outcomes. This includes:
Identifying predictive proteomic and metabolomic signatures for severe NARDS (sNARDS) using longitudinally collected plasma/serum samples.Characterizing the local inflammatory milieu through transcriptomic analysis of tracheal aspirates.Performing a genome-wide association study (GWAS) using genomic DNA from blood to identify genetic variants associated with NARDS susceptibility and severity.

## Methods

3

### Study design and setting

3.1

The SZ-NARDS registry is a prospective, multicenter, observational cohort study, scheduled to run from January 1, 2025, to December 31, 2028. This study will be conducted across nine tertiary-level NICUs in Shenzhen, China, selected for their infrastructure, expertise in neonatal critical care, and patient volume to represent a broad spectrum of care in the region. The study protocol is reported in accordance with the Strengthening the Reporting of Observational Studies in Epidemiology (STROBE) guidelines (30) (Supplementary Material 1). An overview of the study design is provided in Figure 1.

**Figure 1 F1:**
[figure not shown]
Flow chart of the study design, the SZ-NARDS, 2025-2028. Neonates diagnosed with ARDS were enrolled as participants, with clinical measurements and biological specimens collected on day 1, during the acute exacerbation phase (defined by the peak OI), on day 28, and within 24 h before death or initiation of ECMO. Outcome data, including censored cases, will be finalized in 2028 after completing follow-up through clinic visits or phone calls. ARDS, acute respiratory distress syndrome; ECMO, extracorporeal membrane oxygenation; SZ-NARDS, the Shenzhen neonatal acute respiratory distress cohort study; OI, oxygenation index.

Clinical management of patients will remain at the discretion of the local attending physicians according to institutional guidelines, with no study-specific interventions. The study features an open design, allowing for the potential inclusion of additional centers that meet the established criteria during the recruitment period.

### Ethics and participant involvement

3.2

This study was approved by the Ethics Committee of Shenzhen Nanshan Maternal and Child Health Hospital and registered with the Chinese Clinical Trial Registry (ID: ChiCTR2400093854). Each participating center will obtain independent ethics committee approval before commencing recruitment. Participation will be entirely voluntary, and parents or legal guardians will receive comprehensive information on the study's objectives, procedures, and potential implications before providing written informed consent. No patients or members of the public were involved in the initial design or conception of this study.

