### Recruitment, enrollment, and termination

3.5

Recruitment for the SZ-NARDS cohort study will commence on January 1, 2025, at nine hospitals in Shenzhen, Guangdong Province, China. Enrollment and follow-up will be conducted concurrently, with recruitment continuing until the target sample size is achieved. The cohort will be considered complete once all participants have finished the 3-year follow-up period. Research coordinators will provide eligible parents with a detailed study pamphlet and will conduct face-to-face introductions to the cohort. A flowchart of the enrollment process is presented in Figure 2. A participant's active involvement in the study will cease upon death, guardian withdrawal of consent, or confirmed transfer to a non-participating medical facility where follow-up is not feasible.

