#### Inclusion and exclusion criteria

3.6.1

Neonates will be enrolled consecutively upon meeting the full set of Montreux criteria for the diagnosis of NARDS during hospitalization. This cohort will include infants of all gestational ages, including premature infants, provided their respiratory distress meets all five Montreux criteria. These criteria include: (1) an acute onset of symptoms within one week following a known or suspected clinical insult; (2) exclusion of respiratory distress attributable to neonatal respiratory distress syndrome (NRDS), transient tachypnoea of the newborn (TTN), or congenital anomalies; (3) radiological evidence of bilateral, diffuse irregularities, including reduced translucency or opacities, that cannot be explained by conditions such as pleural effusion, atelectasis, NRDS, TTN, or congenital anomalies; (4) absence of congenital heart disease as the cause of pulmonary oedema, with echocardiographic confirmation required to verify the origin of the oedema; and (5) the presence of an oxygenation deficit, categorized by the OI as mild (4 ≤ OI < 8), moderate (8 ≤ OI < 16), or severe (OI ≥ 16). All five criteria must be fulfilled for diagnosis.

Exclusion criteria include: (1) respiratory distress due to primary surfactant deficiency (e.g., hyaline membrane disease), TTN, or congenital lung malformations; (2) congenital heart disease resulting in pulmonary oedema; (3) known genetic syndromes or chromosomal abnormalities; (4) data that did not conform to the Montreux criteria or cases with unavailable outcome data; and (5) abandonment or death occurring within 24 h of birth.

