#### Clinical data and key variable definitions

3.8.1

Demographic characteristics, baseline information, and follow-up data will be systematically recorded following admission and discharge. During hospitalization, data collected will include physical examination findings, neonatal critical illness scores, diagnoses, complications, biochemical parameters, pathogen cultures, imaging results, and treatments administered. Post-hospitalization follow-up assessments will be conducted at designated time points: on day 1 (within 24 h of NARDS diagnosis), during the acute exacerbation phase (defined as the moment when the OI reaches its peak), and on day 28 (or the final day of hospitalization if shorter than 28 days). For patients who succumb to their condition or require ECMO, data will also be gathered 24 h prior to death or the initiation of ECMO. Supplementary data, including hospitalization duration and associated costs, will also be documented.

Key clinical variables were standardized to ensure consistency in reporting:

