### In-hospital outcomes

4.1

Primary in-hospital outcome: composite of mortality or requirement for ECMO within 28 days of NARDS diagnosis.Secondary in-hospital outcomes include: 28-day mortality; 28-day ventilator-free days; duration of invasive mechanical ventilation; incidence of BPD, severe pulmonary hemorrhage, and air leak syndromes; and incidence of significant non-pulmonary organ dysfunction, including hsPDA, NEC (stage ≥ II), and severe IVH (grade ≥ III).

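### The 28-day outcome clock starts at diagnosis, but joining the cohort needs a later approach and written consent; the article does not reconcile the two, so deaths in between would go uncounted and mortality would be biased low

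*Protocol article*

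**What the plan says.** Four parts of the Protocol article bear on when an infant enters the cohort and when counting starts.

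- **Time zero.** Section 4.1 defines the primary in-hospital outcome as a "composite of mortality or requirement for ECMO within 28 days of NARDS diagnosis".
- **Consent.** Section 3.2 makes participation voluntary. Parents are informed of the study's "objectives, procedures, and potential implications before providing written informed consent". Section 3.8.2 asks for a separate consent for biospecimens, so the section 3.2 consent governs the main cohort.
- **Approach.** Section 3.5 states: "Research coordinators will provide eligible parents with a detailed study pamphlet and will conduct face-to-face introductions to the cohort". Eligibility rests on meeting all five Montreux criteria, so the approach follows diagnosis.
- **Enrolment.** Section 3.6.1 states: "Neonates will be enrolled consecutively upon meeting the full set of Montreux criteria for the diagnosis of NARDS during hospitalization". Read literally, this puts entry at diagnosis.

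Two exclusions in section 3.6.1 also touch early deaths: "abandonment or death occurring within 24 h of birth", which runs from birth and not from diagnosis, and "data that did not conform to the Montreux criteria or cases with unavailable outcome data".

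The article does not say when consent must be obtained relative to diagnosis, or what happens to an infant who dies before it is given.

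**The concern.** If membership of the cohort depends on consent, and consent comes after diagnosis, every participant has survived the interval between the two. Infants who die in that interval leave both the numerator and the denominator of 28-day mortality. This is left truncation, and it pushes the mortality estimate down.

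It matters here because the study sets out to establish the true mortality of NARDS in Shenzhen (Abstract) and in China (Discussion), and to explain why a Chinese cohort reported 12.6% when an international one reported 17% to 24%. A downward error of unknown size in the study's own figure weakens that comparison. If centres differ in how quickly they obtain consent, comparisons between centres are distorted as well.

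Nothing else in the article repairs this. Central adjudication (section 5.3) samples enrolled cases and flagged ambiguous ones. Multiple imputation and inverse probability weighting (section 6.1) deal with missing data and loss to follow-up among participants, not with infants who never entered.

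**Working it through.** **The plan's own figure.** Section 3.6.2 asks for 10 events for each of 10 predictors at 12.6% mortality: 100 / 0.126 = 793.65, rounded up to 794. This reproduces.

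**Inputs.** Mortality *m* is taken as 12.6% (section 3.6.2), or as 17% or 24% (Introduction). These are earlier cohorts' figures, used as stand-ins for 28-day mortality. The share *f* of 28-day deaths that precede consent is not in the document. A range of 5% to 20% is assumed.

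**Formula.** Per diagnosed infant, deaths that enter the cohort are *m*(1 − *f*), and infants who enter are 1 − *mf*. Observed mortality is therefore

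*o* = *m*(1 − *f*) / (1 − *mf*).

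Since *m* < 1, *o* is below *m* for every *f* > 0, so the direction does not depend on the assumed range.

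Example, *m* = 0.17 and *f* = 0.20: 0.136 / 0.966 = 0.141.

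| True *m* | *f* = 5% | *f* = 10% | *f* = 20% |
|---|---|---|---|
| 12.6% | 12.05% | 11.48% | 10.34% |
| 17% | 16.29% | 15.56% | 14.08% |
| 24% | 23.08% | 22.13% | 20.17% |

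**Against sampling error.** At 12.6% and n = 1,000, the 95% half-width is 1.96 × √(0.126 × 0.874 / 1,000) = 2.06 percentage points. The shortfall is 0.55 points at *f* = 5%, 1.12 at 10% and 2.26 at 20%. It reaches the size of sampling error only near the top of the assumed range.

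**Against the event target.** With a true 12.6%, 1,000 enrolled infants give about 120, 115 and 103 deaths at *f* = 5%, 10% and 20%. The count falls below 100 once *f* exceeds (0.126 − 0.100) / (0.126 × 0.900) = 22.9%. Within the assumed range, the requirement in section 3.6.2 is still met.

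**What consent delay would give such an *f*.** This needs a further assumption: half of deaths have a mean time of 2 days and half of 10 days, among deaths within 28 days. If consent is spread evenly over the first 12 h, *f* is about 7.2%, and a true 17% is seen as 16.0%. If it is spread evenly over the first 24 h, *f* is about 13.5%, and 17% is seen as about 15.1%. Neither the death-time pattern nor the delay is in the document.

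**The case against.** The strongest reply is that the article does not fix entry after consent. Section 3.2 sets no order between consent and enrolment, section 3.6.1 says "Neonates will be enrolled consecutively upon meeting the full set of Montreux criteria", and the Figure 1 caption likewise describes diagnosed neonates as enrolled. A deferred-consent rule, a waiver or a screening log may stand in the full protocol or the centres' ethics approvals, which are not shown. This stands in part. A reader might infer that infants enter only after consent and that deaths in the gap are never counted, but the documents do not establish that. They do contain two statements about entry that cannot both hold literally when consent is voluntary and sought from parents of infants already eligible.

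Four further limits stand.

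- **Size.** A reader might infer that this mechanism could by itself turn 17% into 12.6%. That needs *f* = (0.17 − 0.126) / (0.17 × 0.874) = 29.6%. Under the death-time pattern assumed above, an exponential consent delay with a median of 24 h gives only about 28%. Half of families would then consent later than 24 h, which fits poorly with baseline data due "on day 1 (within 24 h of NARDS diagnosis" and consented specimens due in the same window (section 3.8.2.2). The 12.6% and 17% to 24% also come from earlier studies, so a bias in this cohort cannot explain the difference between them.
- **Overlap.** Some of these deaths fall within 24 h of birth and are already excluded. That exclusion does not cover an infant diagnosed at several days of age who dies within hours.
- **The composite.** An infant who starts ECMO before consent and survives to enrolment is still counted from diagnosis. The composite is affected through deaths, not through ECMO as such.
- **Analysis.** Section 6.1 gives logistic regression for associations and predictors, not as the estimator of 28-day risk. It neither causes nor corrects the problem.

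**Conclusion.** The concern holds as an unreconciled entry time with a known direction of bias and an unknown size. Outcomes are counted from diagnosis, the described route into the cohort runs through a later approach and written consent, and the statement of enrolment at diagnosis does not settle which governs. Under the stated procedure, deaths before consent would not be counted, so 28-day mortality, and the composite through its death component, would be too low.

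For illustration, with 5% to 20% of deaths before consent, a true 17% is seen as about 16.3% to 14.1%. That range is an assumption, partly overlaps with the exclusion of deaths within 24 h of birth, and shrinks towards nothing if consent is rapid. The documents do not support a claim that gap deaths are certainly lost, that the bias accounts for the published mortality gap, or that the event target fails. The point still deserves correction, because the mortality level is itself a main result of the study.

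**What to change.** 1. Reconcile sections 3.2, 3.5, 3.6.1 and 4.1 by stating when an infant enters the cohort, and how death or ECMO before consent is handled.
2. Record the date and time of diagnosis and of consent for every participant.
3. With ethics approval, keep an anonymous count of all Montreux-positive infants not enrolled, giving the reason (including death before approach) and 28-day death or ECMO status.
4. Report the primary in-hospital outcome for all eligible infants beside the figure for the consented cohort.

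Do not replace the primary estimate with a left-truncated analysis that starts at consent. It would drop ECMO events that precede consent, which the current definition counts, and it assumes that the timing of consent is unrelated to prognosis, which is doubtful in critically ill neonates.

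The cost is two date-time fields, a small log, a line in each centre's ethics submission, and possibly a less favourable mortality figure. The log should run during recruitment, since deaths before approach may be hard to recover later.

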### Dissemination plan

3.3

The findings of this study will be disseminated through a multi-channel strategy aimed at both the public and the scientific community. Results will be shared with participating hospitals and the public via institutional health education platforms and social media. For the scientific community, outcomes will be presented at national academic conferences and submitted for peer-reviewed publication in reputable pediatric journals.

### Confidentiality

3.4

To ensure the confidentiality of study participants, all documents related to the study will utilize a unique, site-specific participant identification number. All identifiable information will be stored separately from clinical data in a secure, encrypted, access-controlled database. The linkage file will be accessible exclusively to authorized site personnel.

### Recruitment, enrollment, and termination

3.5

Recruitment for the SZ-NARDS cohort study will commence on January 1, 2025, at nine hospitals in Shenzhen, Guangdong Province, China. Enrollment and follow-up will be conducted concurrently, with recruitment continuing until the target sample size is achieved. The cohort will be considered complete once all participants have finished the 3-year follow-up period. Research coordinators will provide eligible parents with a detailed study pamphlet and will conduct face-to-face introductions to the cohort. A flowchart of the enrollment process is presented in Figure 2. A participant's active involvement in the study will cease upon death, guardian withdrawal of consent, or confirmed transfer to a non-participating medical facility where follow-up is not feasible.

**Figure 2 F2:**
[figure not shown]
Enrolment campaign flow diagram, the SZ-NARDS, 2025-2028. Phase I: Recruitment of neonates diagnosed with ARDS; Phase II: Hospitalization follow-up, with data collection on day 1, during the acute exacerbation phase (defined by the peak OI), on day 28 (or the final hospital day if the stay was shorter), and within 24 h before death or initiation of extracorporeal membrane oxygenation (ECMO), if applicable; Phase III: Post-discharge follow-up conducted over three years according to Chinese guidelines for high-risk infants. ARDS, acute respiratory distress syndrome; ECMO, extracorporeal membrane oxygenation; SZ-NARDS, Shenzhen neonatal acute respiratory distress cohort study.

### Study participants and sample size

3.6

#### Inclusion and exclusion criteria

3.6.1

Neonates will be enrolled consecutively upon meeting the full set of Montreux criteria for the diagnosis of NARDS during hospitalization. This cohort will include infants of all gestational ages, including premature infants, provided their respiratory distress meets all five Montreux criteria. These criteria include: (1) an acute onset of symptoms within one week following a known or suspected clinical insult; (2) exclusion of respiratory distress attributable to neonatal respiratory distress syndrome (NRDS), transient tachypnoea of the newborn (TTN), or congenital anomalies; (3) radiological evidence of bilateral, diffuse irregularities, including reduced translucency or opacities, that cannot be explained by conditions such as pleural effusion, atelectasis, NRDS, TTN, or congenital anomalies; (4) absence of congenital heart disease as the cause of pulmonary oedema, with echocardiographic confirmation required to verify the origin of the oedema; and (5) the presence of an oxygenation deficit, categorized by the OI as mild (4 ≤ OI < 8), moderate (8 ≤ OI < 16), or severe (OI ≥ 16). All five criteria must be fulfilled for diagnosis.

Exclusion criteria include: (1) respiratory distress due to primary surfactant deficiency (e.g., hyaline membrane disease), TTN, or congenital lung malformations; (2) congenital heart disease resulting in pulmonary oedema; (3) known genetic syndromes or chromosomal abnormalities; (4) data that did not conform to the Montreux criteria or cases with unavailable outcome data; and (5) abandonment or death occurring within 24 h of birth.

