Post-Discharge Follow-Up (Up to 36 months)	For deceased infants: date and primary cause of death For survivors: occurrence of major complications (e.g., severe neurodevelopmental impairment, chronic respiratory morbidity, growth restriction) For lost cases: date and reason for loss to follow-up

aEEG, amplitude integrated electroencephalogram; ARDS, acute respiratory distress syndrome; CRP, C-reactive protein; CT, computed tomography; ECMO, extracorporeal membrane oxygenation; HFOV, high-frequency oscillatory ventilation; MRI, magnetic resonance imaging; OI, oxygenation index; PBMC, peripheral blood mononuclear cells; PCT, procalcitonin.

a Wechat (Tencent Inc., Shenzhen, China) is a widely used social communication application in China, functionally similar to WhatsApp.

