### Post-discharge follow-up outcomes

4.2

Primary follow-up outcome: survival status at 36 months corrected age.Secondary follow-up outcomes: NDI, SRM, growth restriction, and loss to follow-up rates (evaluated at the 24- and 36-month assessments).

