### Statistical analysis plan

6.1

Continuous variables will be summarized as mean ± standard deviation (SD) or median with interquartile range (IQR), depending on distribution. Categorical variables will be presented as frequencies and percentages. Group comparisons will be conducted using the student's *t*-test or Mann–Whitney *U* test for continuous variables, and the *χ*² test or Fisher's exact test for categorical variables.

Univariate logistic regression will be used to examine associations between NARDS and study outcomes. Multivariable logistic regression will then be performed to identify independent predictors. Missing data will be addressed primarily using multiple imputation by chained equations (MICE), assuming data are missing at random. Variables with excessive missingness will be excluded according to predefined thresholds, and the imputation model will be structured accordingly. Sensitivity analyses will include complete-case analysis, k-nearest neighbors (k-NN) imputation, and inverse probability weighting to evaluate the robustness of findings to loss to follow-up. A two-sided *p* < 0.05 will be considered statistically significant. All analyses and visualizations will be conducted using R software (version 4.3.3).

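### Two exclusion rules remove eligible infants because of later events: dropping early deaths lowers observed mortality, and dropping unknown outcomes biases it in an unknown direction and conflicts with the missing-data plan

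*Protocol article*

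**What the plan says.** All references are to the protocol article.

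- **Entry rule (3.6.1).** "Neonates will be enrolled consecutively upon meeting the full set of Montreux criteria for the diagnosis of NARDS during hospitalization".
- **Exclusion (4) (3.6.1).** "data that did not conform to the Montreux criteria or cases with unavailable outcome data". The first half checks eligibility. The second half depends on whether an outcome was later recorded, and the text does not say which outcome.
- **Exclusion (5) (3.6.1).** Running on from the last words of (4): "cases with unavailable outcome data; and (5) abandonment or death occurring within 24 h of birth". The clock runs from birth, not from diagnosis. Abandonment is not defined.
- **What the study is for.** The Abstract and Introduction make the contrast between 12.6% mortality in a Chinese cohort and 17%–24% in an international one the question to resolve, and hypothesise about the true incidence and mortality in Shenzhen. Death is part of the primary in-hospital outcome (4.1), and survival is the primary follow-up outcome (4.2).
- **How lost infants are treated elsewhere.** Section 4.2 lists "loss to follow-up rates (evaluated at the 24- and 36-month assessments" as a secondary outcome. Table 1 (3.8) collects "For lost cases: date and reason for loss to follow-up". The Figure 1 caption says the final outcome data include censored cases. Section 6.1 plans multiple imputation (MICE) and, as a sensitivity analysis, "inverse probability weighting to evaluate the robustness of findings to loss to follow-up". Under 3.5, active involvement ends on "confirmed transfer to a non-participating medical facility where follow-up is not feasible", which is termination of participation rather than exclusion.

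**The concern.** An infant can meet all five criteria and only afterwards die, be abandoned or end up without a recorded outcome. Removing that infant makes membership of the cohort depend on the outcome, or on whether the outcome was observed. For most descriptive variables this would be a nuisance. Here the mortality rate is the quantity the study wants to estimate and compare with published cohorts, so the selection acts directly on the headline result.

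Very early deaths among eligible infants are plausible, since 3.8.4 names meconium aspiration and perinatal asphyxia among the causes. Nothing in the article counts these infants separately or says whether the comparison cohorts applied the same rule. The limitations paragraph in section 7 discusses selection bias only in terms of geography and affluence. A reader of the results could therefore not tell how much of any difference in mortality comes from the exclusions.

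The missing-outcome clause raises a further problem of consistency: an infant excluded for lacking an outcome cannot also be censored, counted as lost, imputed or weighted for that outcome.

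**Working it through.** **Inputs.** Mortality of 12.6% and a target of 1,000 infants come from 3.6.2. The article gives no count of very early deaths, of infants with unknown outcome, or of mortality among them, so those are assumed ranges.

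**The plan's own figure.** 10 events per predictor × 10 predictors = 100 deaths; 100 / 0.126 = 793.65, rounded up to 794. This agrees with 3.6.2.

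**Base case (assumption).** 1,000 retained infants with 126 deaths, so the study would report 12.6%.

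**Exclusion (5), deaths.** Restoring x excluded deaths gives (126 + x) / (1000 + x):

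| x | calculation | mortality |
|---|---|---|
| 5 | 131 / 1005 | 13.0% |
| 10 | 136 / 1010 | 13.5% |
| 20 | 146 / 1020 | 14.3% |

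Each restored infant is a death, so the rate rises for every x above 0. The direction is certain; only x is unknown. Incidence falls for the same reason, because these cases leave its numerator.

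**Exclusion (4), unknown outcomes.** Restoring u infants whose mortality is q gives (126 + uq) / (1000 + u). With u = 50:

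| q | calculation | mortality |
|---|---|---|
| 0 | 126 / 1050 | 12.0% |
| 12.6% | 132.3 / 1050 | 12.6% |
| 30% | 141 / 1050 | 13.4% |
| 50% | 151 / 1050 | 14.4% |
| 100% | 176 / 1050 | 16.8% |

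The exclusion lowers reported mortality only if q exceeds the mortality of the retained infants. If the unknowns are mainly survivors, which could well be so at 36 months, it raises it.

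**Abandonment.** The same formula applies, with q the mortality of abandoned infants. Without a definition and vital status, q is unknown.

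**Both rules together.** With x = 20 and u = 50, the rate is 146 / 1070 = 13.6% (q = 0) to 196 / 1070 = 18.3% (q = 100%). With x = 5, u = 100 and q = 0, it is 131 / 1105 = 11.9%, so the net direction can reverse.

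**Consistency of the text.** Exclusion (4) removes infants without outcome data. Section 4.2 counts the lost, Table 1 dates and explains each loss, the Figure 1 caption keeps censored cases, and 6.1 weights for loss to follow-up. If the clause covers outcomes to 36 months, it conflicts with all four. If it covers only in-hospital outcomes, the conflict with long-term follow-up narrows, but the 28-day primary outcome is still restricted to infants in whom it was observed.

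**The case against.** A 24-hour survival threshold can be seen as a choice of target population. Section 6.5 relies on surfactant response and clinical course to separate NARDS from NRDS, and these are harder to judge in an infant who dies that early. If the earlier cohorts used the same threshold, keeping it helps comparability. Every death after 24 h of age stays in, so the number affected may be small. This argument stands as a reason to report the restricted rate as well. It does not justify leaving the excluded infants uncounted.

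Four stronger readings are tempting, and the article does not support them:

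- **Both exclusions lower mortality.** This is certain only for early deaths. Unknown outcomes can act either way, and abandonment depends on vital status.
- **The exclusions could produce the whole gap between 12.6% and 17%.** Arithmetically, 53 restored deaths give 179 / 1053 = 17.0%. That would place 53 of 179 deaths (30%) in the first 24 h of life among infants who had already met all five criteria, and nothing in the article supports this. The published gap also lies between two earlier cohorts, so this study's rules cannot have caused it.
- **Loss to follow-up becomes zero and imputation and weighting have nothing to act on.** This needs the harshest reading of the missing-outcome clause. Other sections plainly expect lost infants to remain, and imputation also serves missing covariates.
- **The sample size is undermined.** The exclusions do not enter 100 / 0.126, recruitment continues to target (3.5), and 1,000 infants yield 100 deaths even at 10.0% mortality. Restoring early deaths would add events.

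**Conclusion.** The concern holds in a limited form. Section 3.6.1 selects on events after eligibility, and this bears on the study's central quantity.

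For deaths within 24 h of birth, the effect on observed mortality and incidence is downward and of unknown size: from 12.6% to 13.0%, 13.5% or 14.3% if 5, 10 or 20 such deaths per 1,000 retained infants were restored. For unknown outcomes the direction is itself unknown (12.0% to 16.8% if 50 were restored), and for abandonment it depends on vital status. All of these counts are assumptions. Whether the comparison with earlier cohorts is distorted also depends on whether those cohorts applied the same rule, which the article does not say.

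Separately from any numbers, the missing-outcome clause is inconsistent with sections 4.2 and 6.1, Table 1 and the Figure 1 caption, and needs to be reconciled with them.

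**What to change.** 1. Delete the missing-outcome clause from exclusion (4) and keep the half on conformity with the Montreux criteria.
2. Keep every eligible infant in the denominator. Handle unknown outcomes with the MICE and inverse probability weighting already planned, and add best-case and worst-case bounds for death or ECMO within 28 days.
3. Count infants who met the Montreux criteria before death or abandonment within 24 h of birth in incidence and mortality, using a minimal dataset where consent and ethics approval allow.
4. Define abandonment, record vital status, and show mortality with these infants treated as deaths and as censored.
5. Report the rate excluding the infants in item 3 as a sensitivity analysis for comparison with earlier cohorts.

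**Cost.** An amendment to two criteria and a short data form. These infants will have more missing covariates and specimens. Very early deaths raise a real consent question, because 3.2 requires written guardian consent and ethics approval at each centre. The change is best made during recruitment, since early deaths that were never recorded may not be recoverable later.
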